## Abstract

**Introduction:**

Cervical cancer (CC) is the most common cancer and accounts for one quarter of all cancer-related deaths among women in Uganda, where lifetime CC screening is estimated to be as low as 5%. This study will evaluate the feasibility, acceptability, and preliminary efficacy of a social network-based group intervention designed to empower women who have received CC screening to encourage women in their social network to also screen.

**Methods:**

Forty adult women (index participants) who have recently screened for CC will be recruited, 20 of whom will be randomly assigned to take part in the intervention and 20 to the wait-list control. Each index participant will be asked to recruit up to three female social network members (i.e., alters; maximum total = 120 alters) who have not screened for CC to participate in the study. Assessments (survey and chart abstraction) will be administered at baseline and month 6 to index and alter participants. The primary outcome is CC screening among participating alters, with a secondary outcome being engagement in CC prevention advocacy among index participants. Repeated-measure multivariable regression analyses will be conducted to compare outcomes between the intervention and control arms.

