## Methods

### Study design

This study will pilot test a social network-based group intervention that aims to empower and mobilize women who have been screened for CC to advocate for CC screening and treatment in female members of their social network (referred to as “alters”). We will pilot the intervention in a randomized controlled trial of 40 women who have been screened for CC (referred to as index participants), with 20 randomly assigned to receive the intervention (in two groups of 10) and 20 to the wait-list control [(each evenly stratified by age (under and over age 35) and history of CC-related treatment)]. Individual randomization entails risks for contamination, but statistical models suggest that ≥ 30% of the control arm must receive the equivalent of a full-strength intervention to result in meaningful contamination [24]. We opted for the wait-list control rather than an attention control, because this provides clearer findings for policy makers when considering intervention effects, and adequate control for attention may not be feasible given the 2-h duration and group dynamics of the workshops. The control arm receives the intervention after the completion of month-6 follow-up assessments. There is no way to blind the participants on whether or not they receive the intervention; this could potentially influence the outcomes, as clients may feel more or less incentivized to perform well in light of whether or not they receive the intervention. We do not see a way to prevent this potential bias, nor a way to distinguish such effects from actual intervention effects, but this limitation will be cited in reports of study findings. Data will be collected at baseline and month 6 from index participants and up to three alters of each index participant (max. total = 120 alters) who have not previously screened for CC. The primary outcome is alter CC screening over the 6-month follow-up period; secondary outcomes are index participant reported engagement in CC screening advocacy, internalized CC stigma, and disclosure of CC screening experience.

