### Participants

Women are eligible to enroll as index participants if they are age 18 years or older, have screened for CC within the past year, have stable health status (i.e., not in end stages of disease), and shared their CC screening experience with at least one alter who is perceived to not have screened for CC in the past 3 years. Alter participants are eligible if they are at least 18 years of age, are recruited by an index participant, and report never being screened for CC.

Index participants will be recruited through the RHHJ database of women who have received CC screening and referral from Buyinja and Banda providers who have screened women for CC. An RHHJ staff member or health center provider will inform eligible women of the study, and those who express interest in participating will be referred to the study coordinator for formal eligibility screening and implementation of consent procedures. Women who provide written informed consent will then be administered the baseline assessment and be randomly assigned to the intervention or control arm. To recruit alters, we will use data collected from the baseline survey assessment of female social network members to randomly select 5 alters who know the participant’s CC screening experience (or as many as there are if < 5) and ask the participant if she is comfortable asking 3 of these alters to participate. The index participant will be asked to call each selected alter at the end of the interview to describe the study in the presence of the coordinator, who will schedule a study visit for alters who express interest in participating. If an alter refuses or cannot be reached, a replacement will be randomly selected from the list of alters who know the index participant’s CC screening experience.

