### Statistical analysis

To assess feasibility and acceptability, we will examine recruitment (percent of screened women and social network members who are approached to participate, decide to enroll), retention, workshop attendance, and participant feedback elicited in the process measures. To assess intervention effects on alter CC screening, *w*e will use an intent-to-treat approach. In addition to comparing the arms at each time interval (baseline, month 6), we will apply logistic generalized mixed models to our repeated-measure data to examine intervention effects, using an indicator for study arm, and time by arm interaction to indicate whether change differs between the arms. We will use imputation for item nonresponse and attrition weights to account for nonrandom dropouts using logistic regressions; if dropout is random, analyses will incorporate design effects. We will explore the sensitivity of significance levels and conclusions to a range of plausible ICC values (.005 to .05) for the outcomes. We will control for and examine interaction effects with intervention process variables (e.g., number of workshops completed) and characteristics of the index participant (e.g., age), as well as the alter (e.g., position in the network, knowledge of index participant’s CC risk).

We will explore factors that may mediate the intervention effects on the primary outcomes among variables targeted by the intervention*,* such as internalized CC stigma, disclosure (percentage of alters disclosed to), and engagement in CC screening advocacy. The sample size may be too small to do mediation analysis, but we will examine how potential mediators are associated with the primary outcomes and treatment condition using bivariate statistics.

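### No baseline adjustment is stated for the index-level outcomes; if the article's one repeated-measure model (arm plus time by arm) is used for them, precision is given away with 20 women per arm

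*Protocol article*

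**What the plan says.** The Abstract (Methods) sets the design for index women as "20 of whom will be randomly assigned to take part in the intervention and 20 to the wait-list control". On data collection it says "Assessments (survey and chart abstraction) will be administered at baseline and month 6 to index and alter participants", so each index outcome has two measurements. It names alter screening as primary and index advocacy as secondary, and the next sentence is "Repeated-measure multivariable regression analyses will be conducted to compare outcomes between the intervention and control arms".

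Under Study design, "secondary outcomes are index participant reported engagement in CC screening advocacy, internalized CC stigma, and disclosure of CC screening experience". Table 1 lists advocacy as a secondary outcome but puts internalised stigma and disclosure under potential mediators. Study design also says that the arms are stratified by age (35 as the cut) and by history of CC-related treatment.

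The Participants section describes consented women being "administered the baseline assessment and be randomly assigned to the intervention or control arm", in that order.

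The Statistical analysis section opens its modelling text with "To assess intervention effects on alter CC screening". It plans arm comparisons at baseline and at month 6, with no adjustment mentioned. It then adds logistic mixed models "using an indicator for study arm, and time by arm interaction to indicate whether change differs between the arms". The covariates listed are process variables and characteristics of the index woman and the alter. The baseline value of the outcome is not among them.

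**The concern.** Advocacy, stigma and disclosure in index women are measured before allocation, so the expected baseline means are equal in the two arms. A model with a free arm effect at baseline plus a time-by-arm term does not use that fact. It subtracts the observed baseline difference in full, although that difference is only chance. Regression on the baseline value, or a mixed model that holds the baseline means equal, subtracts only as much of it as the correlation warrants.

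The index outcomes rest on at most 40 women. The Sample size section says that the pilot is meant to supply effect sizes and other parameters for a larger trial. Intervals wider than the data require weaken that output, and the information needed to narrow them is already being collected.

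**Working it through.** **The article's own figure.** There is none for index outcomes. For the primary alter outcome: 120 × 0.9 / 2 = 54 per arm, divided by 1 + (3 − 1) × 0.01 = 1.02, gives 52.9 (stated: 53). Power for 5% against 24% at 53 per arm, two-sided 5%, is 80.2%. The figure reproduces and is not in dispute.

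**Inputs for the index outcomes.** From the article: 20 women per arm, two visits, alpha 0.05, power 80%. Assumed: a two-sided test, a continuous score with the same SD at both visits, independent women, and a baseline to month-6 correlation r, which the article does not give (0.3 to 0.9 shown).

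**Variance factors, in units of SD².**
- Month-6 values alone: 1
- Change score, or unconstrained time by arm: 2(1 − r)
- Baseline-adjusted (ANCOVA): 1 − r²
- Ratio of adjusted to change: (1 − r²) / [2(1 − r)] = (1 + r)/2

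**Is time by arm really the change score here?** In 300 simulated trials (20 per arm, r = 0.5), the arm-by-time estimate from a random-intercept linear model equalled the difference in mean change to within 1e-14. The SD of the estimate was 0.312, against 0.260 for ANCOVA and 0.261 for a mixed model with a common baseline mean. Theory gives 0.316 for change and 0.274 for ANCOVA.

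**Detectable difference** at 20 per arm, normal approximation: (1.960 + 0.842) × √(2/20) × √factor = 0.886 × √factor, in SD. The last column is 20 divided by the ratio.

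| r | Change | Adjusted | Variance ratio | n per arm for change to match adjusted at 20 |
|---|---|---|---|---|
| 0.3 | 1.05 | 0.85 | 0.65 | 30.8 |
| 0.5 | 0.89 | 0.77 | 0.75 | 26.7 |
| 0.7 | 0.69 | 0.63 | 0.85 | 23.5 |
| 0.9 | 0.40 | 0.39 | 0.95 | 21.1 |

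Month-6 values alone give 0.89 SD at every r, so below r = 0.5 the change contrast is less precise than ignoring baseline. For an assumed true effect of 0.8 SD, power is 57% (change) against 76% (adjusted) at r = 0.3, 72% against 83% at r = 0.5, and 90% against 94% at r = 0.7.

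**With loss to follow-up.** The article's 10% attrition is stated for alters only. If it also held for index women (18 per arm), the non-central t, with one degree of freedom charged for the covariate, gives 1.14 against 0.92 SD at r = 0.3, 0.96 against 0.83 at r = 0.5, and 0.75 against 0.69 at r = 0.7.

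**Against the better of the two analyses described.** The Statistical analysis section also plans a month-6 comparison. Up to r = 0.5 that is the better of the two, and adjustment leaves 1 − r² of its variance (0.91 at r = 0.3, 0.75 at r = 0.5). From r = 0.5 upward change is better, and adjustment leaves (1 + r)/2. For r between 0 and 1, the most that adjustment saves against the better one is therefore 25% of variance, at r = 0.5.

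**The case against.** A reader might infer that the plan states that index outcomes will be analysed by change. It does not. The time-by-arm wording is introduced for alter screening and belongs to a logistic model: a different outcome, unit and scale. The Abstract sentence covers outcomes in the plural straight after naming index advocacy, so some repeated-measure model is meant for that outcome, but its form is left open. The term repeated-measure does not exclude a common baseline mean, which would be as precise as ANCOVA. A full protocol or analysis plan not shown may settle the matter. All of this stands, and it makes the application to index outcomes an inference.

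It also stands that time by arm would not be the only analysis. If the Statistical analysis text extends to index outcomes, so does its month-6 comparison, though that is unadjusted as written.

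The size of the loss is open to challenge too. Advocacy is recorded alter by alter over 12 named women, who may differ at follow-up, and disclosure is a percentage of alters. For these the formulas are only approximate, and in a logistic mixed model the equality with change scores does not hold. The intervention is given in two groups of 10. Group variance arising after baseline would add the same amount to both variances, which moves the ratio towards 1 and makes the detectable differences above too small.

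The objection does not remove the core. The one repeated-measure model described leaves baseline means free, and no text adjusts an index outcome for its baseline.

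**Conclusion.** The point holds as an efficiency remark with moderate confidence. The algebra is firm; its application to the index outcomes is inferred. If the described model is used for a score-type index outcome, baseline adjustment cuts the variance of the effect estimate by 35%, 25%, 15% and 5% at r = 0.3, 0.5, 0.7 and 0.9. This rests on an assumed correlation, equal variances at the two visits and no workshop-group clustering. It applies directly to internalised stigma and roughly to advocacy and disclosure.

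A reader might go further and conclude that the index results would be biased or that a stated figure is wrong. The documents support neither. Under randomisation the change contrast is unbiased, the article makes no power claim for index outcomes, and it says openly that the small sample limits power. The primary outcome's sample size is unaffected.

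**What to change.** State in the Statistical analysis section that, for the index-level secondary outcomes, the effect measure is the arm difference at month 6 adjusted for the woman's own baseline value, by ANCOVA or by a mixed model with a common baseline mean. Include the two stratification factors (age group and history of CC-related treatment), and use a link suited to outcomes that are counts or proportions. The time-by-arm term with free baseline means should not serve as the effect measure for these outcomes. If a full analysis plan already says this, a matching sentence in the article is enough.

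The cost is wording and a few degrees of freedom. No added data, visits or participants are needed.

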**Discussion:**

If successful, this intervention model has the potential not only to impact uptake of CC screening and treatment but also to establish a paradigm that can be applied to other health conditions.

**Trial registration:**

NIH Clinical Trial Registry NCT04960748 (clinicaltrials.gov).

## Introduction

Cervical cancer (CC) is the most common cancer and accounts for ~25% of all cancer-related deaths among women in Uganda, who have one of the highest incidence rates in the world at 54.8 per 100,000 [1–3]. CC screening via visual inspection of cervix with acetic acid (VIA), and thermal therapy for precancerous lesions, is available for free or a low cost in Uganda, while radiotherapy is prescribed for advanced disease but sub-optimally available due to high patient load and still too costly for most women to access, despite the subsidies. This highlights the importance of screening to prevent onset of cancerous lesions, yet most (80%) Ugandan women have advanced CC disease (stage 3 or higher) at initial presentation for care [4], and it is estimated that just 5% of women have ever screened for CC [4–6].

A key structural barrier to uptake of CC screening has been poor access [7], but national government initiatives are underway to ramp up availability, especially screening and early-stage treatment [8]. Nonstructural barriers to screening include lack of awareness and misinformation, embarrassment with the screening procedure (especially if the provider is male), and fear of screening results [6, 7, 9, 10]. Stigma associated with CC being a sexually transmitted infection, and the degrading symptoms of advanced disease (e.g., offensive discharge, heavy bleeding, fistulas, incontinence) that often lead women to be isolated and feel ashamed [6, 7, 9, 10], may be impediments to treatment more so than screening. Facilitators to screening include outreach services, support and encouragement from others, and knowing someone who has been screened or diagnosed [6, 7]; however, no studies have tried to leverage and diffuse information through social networks to improve uptake of screening or treatment [7].

One promising approach is to empower women who have personal experience with being screened for CC, and treated if applicable, to act as advocates, and to encourage other women they know to get screened. Building on theories of social diffusion [11], cognitive consistency [12], and social influence [13], which posit that behavior change can be initiated by a few and diffused to others through modeling, advocacy, and shifts in social norms, peer advocacy interventions have been shown to promote prevention and screening, raise awareness, and reduce stigma in the context of HIV [14–16]. In the context of CC, peer education has been evaluated at the level of healthcare workers [17], male partners [18], and women at risk [10], but not through social networks. We recently developed and tested a network-based advocacy group intervention, *Game Changers*, that mobilized people living with HIV in Uganda to act as change agents for HIV prevention within their social networks [19]. The intervention, which targeted reduction of internalized stigma, disclosure skills, healthy living, and advocacy skills building, resulted in reduced HIV stigma, increased HIV disclosure and engagement in advocacy among the participants, and increased HIV testing and condom use among their network members [19].

We believe these same processes are relevant to empowering women who have screened for CC to act as change agents for CC prevention and treatment. We believe that effective advocacy first requires coping with internal and external stigma, particularly if screening resulted in evidence of infection and need for treatment, and achieving a level of self-acceptance. Self-acceptance facilitates comfort with sharing one’s screening experience with others and being able to receive support from others. Sharing one’s experience of screening raises the credibility of one’s advocacy for CC screening and treatment and better enables successful encouragement of others to seek screening and treatment (if needed). However, disclosure of CC risk can have both positive (increased support) and negative (rejection, ridicule, shame) outcomes, so disclosure of decision-making skills is important. To be effective advocates, women must model the behaviors they encourage others to adopt, by prioritizing healthy living including adherence to CC rescreening schedules. Lastly, learning communication skills and strategies for when, how, and who to engage with advocacy, is key to effective advocacy. These processes make up the framework (Fig. 1) guiding the intervention we are testing in this study. It draws on existing evidence-based network-driven interventions in the context of HIV prevention [20–23] and mechanisms such as experience sharing and role playing to foster peer support.

**Fig. 1 Fig1:**
[figure not shown]
Conceptual framework for promotion of cervical cancer (CC) prevention advocacy among screened women to affect CC screening among social network members

We will conduct a randomized, controlled pilot of the intervention to evaluate the feasibility, acceptability, and preliminary efficacy of the intervention to increase CC screening among women in the social networks of the intervention recipients. The protocol for this trial is described in detail in this paper. If results are promising, this pilot study will inform a more robust evaluation of the intervention in a larger trial. This intervention model has the potential not only to impact uptake of CC screening and treatment but also to establish a paradigm that can be applied to other health conditions.

## Methods

### Study design

This study will pilot test a social network-based group intervention that aims to empower and mobilize women who have been screened for CC to advocate for CC screening and treatment in female members of their social network (referred to as “alters”). We will pilot the intervention in a randomized controlled trial of 40 women who have been screened for CC (referred to as index participants), with 20 randomly assigned to receive the intervention (in two groups of 10) and 20 to the wait-list control [(each evenly stratified by age (under and over age 35) and history of CC-related treatment)]. Individual randomization entails risks for contamination, but statistical models suggest that ≥ 30% of the control arm must receive the equivalent of a full-strength intervention to result in meaningful contamination [24]. We opted for the wait-list control rather than an attention control, because this provides clearer findings for policy makers when considering intervention effects, and adequate control for attention may not be feasible given the 2-h duration and group dynamics of the workshops. The control arm receives the intervention after the completion of month-6 follow-up assessments. There is no way to blind the participants on whether or not they receive the intervention; this could potentially influence the outcomes, as clients may feel more or less incentivized to perform well in light of whether or not they receive the intervention. We do not see a way to prevent this potential bias, nor a way to distinguish such effects from actual intervention effects, but this limitation will be cited in reports of study findings. Data will be collected at baseline and month 6 from index participants and up to three alters of each index participant (max. total = 120 alters) who have not previously screened for CC. The primary outcome is alter CC screening over the 6-month follow-up period; secondary outcomes are index participant reported engagement in CC screening advocacy, internalized CC stigma, and disclosure of CC screening experience.

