#### Sample size

The small sample limits statistical power, but our goal is to assess the preliminary effect size and other parameters to inform a future larger trial. Assuming 120 alters enroll, attrition rate of 10% among alters (we have retained 90–94% over 12 months in past studies in Uganda) [25, 26], *ICC* = .01 to control for clustering within the alters of each participant, and a 5% rate of receiving CC screening in control alters, the effective sample size will be 53 per arm, enabling us to detect a medium effect size (Cohen’s *d* = 0.57; 19 percentage point difference in CC screening among alters during the 6-month follow-up period), with 80% power (alpha = .05). If ICC is as high as .05, and as few as 80 alters enroll, the detectable effect size = 0.72 (25.5 percentage point difference between groups).

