The adapted intervention consists of 7 workshops. *Workshop 1* focuses on *addressing fears and concerns related to CC risk and use of self-compassion and peer support to overcome these fears*, as well as introducing the overall vision for empowering women to become change agents for CC prevention and treatment. With participants feeling more supported, *Workshop 2* focuses on *building skills and decision-making for sharing one’s personal CC screening experience*, knowing to whom to disclose and when and how to initiate and navigate disclosure and conversations about CC. *Workshop 3* builds skills and motivation for *healthy living* so that their own behavior (e.g., good nutrition, periodic VIA screens) is consistent with the behavior they encourage in others, as well as learning facts and myths related to CC to facilitate accurate CC screening advocacy. *Workshop 4* introduces the concept of a social network and how one’s network can serve as a tool for CC prevention advocacy and dissemination of CC-related information. *Workshops 5 and 6* focus on the skills needed for successful *CC-related advocacy*, including strategies for how to start conversations about CC and to keep these discussions going, as well as learning effective communication skills (e.g., reflective listening, paraphrasing, open-ended questions). *Workshop 7* inspires a *commitment to ongoing CC advocacy* through peer solidarity and support. The workshops will be conducted using a structured facilitator manual, in the predominant local languages of Samia and Lusoga, by two trained women from Namayingo who have experience being screened for CC. Using principles of compassion-focused therapy [27], the workshops will be administered in a group format to facilitate the use of *sharing of experiences* to build support, solidarity, and motivation among participants; *group problem-solving* and *role playing* to build skills and self-efficacy; *setting personal goals* regarding healthy living, disclosure, and advocacy; and homework to reinforce practice of new skills and generate personal experiences to be processed in the workshops. The seven workshops will be conducted weekly over 2 months, and each workshop will last 2 h. Participants will receive 30,000 Uganda shillings (~US $8) for attending each workshop to cover transport costs.

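### The 19-point detectable difference allows for clustering of alters within index participant but not within the two workshop groups, so it is somewhat optimistic

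*Protocol article*

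**What the plan says.** Under Study design, the 40 index women are split, with "20 randomly assigned to receive the intervention (in two groups of 10) and 20 to the wait-list control". Controls are offered the workshops only after the month-6 assessment, so they form no groups during follow-up.

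Under Intervention, "the workshops will be administered in a group format to facilitate the use of" shared experience, joint problem-solving and role play, over seven sessions. The group is part of how the intervention is meant to work.

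Under Sample size, the inputs are: "Assuming 120 alters enroll, attrition rate of 10% among alters"; an ICC of .01 "to control for clustering within the alters of each participant"; and "a 5% rate of receiving CC screening in control alters". From these, "the effective sample size will be 53 per arm", and the detectable effect at 80% power is a "19 percentage point difference in CC screening among alters during the 6-month follow-up period". A second scenario, with an ICC of .05 and 80 alters, gives 25.5 points.

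Under Statistical analysis, logistic mixed models with arm and time-by-arm terms are planned, together with a check of conclusions over a "range of plausible ICC values (.005 to .05) for the outcomes". That section does not say at which level the ICC applies.

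**The concern.** Women who attend the same workshop group share facilitators, discussion and peer support. If one group gels better than the other, its members may advocate more, and more of their alters may be screened. Alters linked to the same workshop group are then correlated, even when they belong to different index women. Nothing comparable happens in the control arm. The design is therefore partially nested: individual randomisation, with group-level correlation in one arm only.

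The power statement treats alters of different intervention women as independent. Any positive workshop-group correlation makes the intervention-arm effective sample size smaller than stated. This matters even in a pilot, because the declared purpose is to pass an effect size and other design parameters to a larger trial. If the workshop-group level is overlooked here, the next trial may be sized as if the only clusters were sets of three alters.

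**Working it through.** **Inputs from the article.** 120 alters, 10% attrition, so 108 retained: 54 per arm, 2.7 per index woman and 27 per workshop group (54/2). Index-level ICC .01, control rate 5%, alpha .05, power 80%. Two-sided testing is assumed, because the article does not state sidedness.

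**Input not in the article.** The workshop-group ICC, written g below. I use .005 and .01 as main values and .05 as a pessimistic one.

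**Step 1: reproduce the stated figures.** Index-level design effect = 1 + (2.7 − 1) × .01 = 1.017, so effective n = 54/1.017 = 53.1 per arm. With cluster size 3 it is 54/1.02 = 52.9. Both round to the stated 53.

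Power is that of a pooled two-proportion z-test: Φ[(d − 1.96 × SE0)/SE1], where
- SE0 = √[p̄(1 − p̄)(1/nC + 1/nI)]
- SE1 = √[pC(1 − pC)/nC + pI(1 − pI)/nI]

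For 5% v 24% with 53 per arm, SE0 = 0.0684 and SE1 = 0.0659. Power = Φ[(0.19 − 0.1341)/0.0659] = 80.2%. Solving for 80% gives 18.9 points. The plan's figures are therefore reproduced with index-level clustering alone.

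The second scenario behaves the same way: 80 alters less 10% is 36 per arm, 36/(1 + 1 × .05) = 34.3, and the detectable difference is 25.4 points against the stated 25.5. It too contains no workshop-group component.

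**Step 2: add the workshop group, intervention arm only.** Intervention design effect = 1.017 + (27 − 1) × g. The control arm stays at 1.017 (n = 53.1).

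| g | Design effect | Effective n, intervention | Power at 19 points | Detectable difference |
|---|---|---|---|---|
| 0 | 1.017 | 53.1 | 80% | 18.9 |
| .005 | 1.147 | 47.1 | 78% | 19.5 |
| .01 | 1.277 | 42.3 | 77% | 20.1 |
| .05 | 2.317 | 23.3 | 66% | 24.4 |

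For g = .01: SE0 = 0.0703 and SE1 = 0.0722, so power = Φ[(0.19 − 0.1377)/0.0722] = 76.6%.

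**Step 3: does it matter how the ICCs combine?** Two alters of one intervention woman also share her workshop group, so the index-level .01 may already contain g. The intervention design effect is then 1.017 + (27 − 2.7) × g. At g = .005 and .01 this gives 1.138 and 1.260, with detectable differences of 19.5 and 20.1 points and power of 78% and 77%. The main figures do not change.

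**Step 4: error rate of a test that ignores workshop groups.** This applies only if the groups truly differ while the average effect is zero. The ratio of true to assumed standard error is √[(DE_I + 1.017)/(2 × 1.017)], where DE_I is the intervention design effect. At g = .01 it is √(2.294/2.034) = 1.062, and a nominal 5% test has error of about 6.5%. At g = .05 it is √(3.334/2.034) = 1.280, and the error is about 12.6%. Simulation with beta-binomial group rates, at null screening rates of 5% and 15%, gave 5.8% to 6.6% at g = .01 and 10.6% to 13.1% at g = .05.

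**The case against.** Several points on the other side have force.

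- **The analysis section is silent, not wrong.** A reader might infer that the analysis itself allows for clustering within index participant only. The article does not say so. It plans mixed models, design effects and an ICC sensitivity range without naming a level, and random-effect structure is commonly left to a fuller plan. This stands: only the power statement fixes the level.
- **The large figures do not belong in the headline.** A reader might take 24 points, 66% power and an error above 10% as the expected position. A group ICC of .05 exceeds the base-case within-participant ICC of .01, which should already contain it. The outcome is measured in alters, who are not the workshop attendees, and a structured manual, the same two facilitators and observed sessions should limit variation between groups. This stands: .05 is a pessimistic bound, and the .005 to .05 range in the article is not stated to be a workshop-group range.
- **The 5% error is not necessarily inflated.** If the workshops do nothing at all, the groups do not differ and the error stays near 5%. This stands as a condition on Step 4.
- **Limited power is already admitted.** The article says that the small sample limits power, calls efficacy preliminary and quotes up to 25.5 points. This answers the point only in part. The 25.5 comes from fewer alters and a higher index-level ICC, so neither it nor the general caveat discloses the workshop-group level.

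**Conclusion.** The power statement omits a level of clustering that the design creates. The direction is certain for any positive workshop-group ICC. The size depends on a value that the documents do not give. At an assumed .005 to .01, consistent with the plan's base case, the detectable difference is about 19.5 to 20.1 points rather than 19, and power at 19 points is 78% to 77% rather than 80%. At .05 the figures are about 24 points and 66%.

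The error rate of a test that ignores workshop groups would be about 6% at .01 and about 10% to 13% at .05, provided that the groups truly differ around a zero average effect. These figures use normal theory. With two groups, the between-group variance has one degree of freedom, so even the corrected figures are somewhat favourable. For a pilot the practical effect is modest under the main assumption, but the omission should be put right before its parameters are carried into a larger trial.

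**What to change.** 1. In Sample size, restate the detectable difference as about 19.5 to 20 points, and up to about 24 in a pessimistic case. Give the workshop-group ICC (.005 to .01, and .05) as an assumption.
2. In Statistical analysis, state that the ICC sensitivity analysis also covers workshop groups, by adding (alters per group − 1) × group ICC to the intervention-arm design effect. A fixed range is preferable to relying on an estimated random effect, because two groups cannot support a reliable variance estimate.
3. Report alter screening separately for each workshop group, and say that group effects cannot be separated from the intervention effect in this pilot.

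The cost is a slightly less favourable stated figure, some wording and a small extra calculation. No further participants or data are needed.
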